### Study logic model

A logic model [81] was developed by the evaluation team with inputs from the individuals leading the implementation of APCNF to understand programme activities and select indicators for evaluation (Fig 2). A logic model is a graphical representation of the way the programme is expected to work and links the inputs of the programme with the activities, outputs, outcomes, and impacts [82]. It does not include every detail about the programme but indicates the critically important aspects relevant for programme evaluation.

**Fig 2 pone.0281677.g002:**
[figure not shown]
The BLOOM (co-Benefits of Largescale Organic farming On huMan health) study logic model for the evaluation of the Andhra Pradesh Community-managed Natural Farming programme in India. Abbreviations: EPAC, Evaluation and Policy Advisory Committee; iCRPs, internal Community Resource Persons; MRC, Medical Research Council; RySS, Rythu Sadhikara Samstha; SHGs, self-help groups; UKRI, UK Research and Innovation.

The BLOOM logic model consists of inputs, activities, outputs, outcomes (short-term and medium-term), and impacts. The first three components of the logic model are further divided into two groups–programme-related and evaluation-related. The former describes what is currently present with respect to the APCNF programme whereas the latter describes the additional work the evaluation team is proposing to conduct. The short-term outcomes are changes that the evaluation and implementation teams hypothesise will occur after 12 months of implementation of APCNF whereas the medium-term outcomes are expected after 24 months. Although the implementation team expects other changes due to the APCNF programme, we have chosen to present those which are agreed upon by both the evaluation and implementation teams.

### Study design

This study is a community-based, cluster-randomised controlled evaluation with two parallel groups: APCNF (‘intervention’) versus conventional practices (‘control’). A total of 80 clusters will be randomly allocated 1:1 to intervention or control. The study will run for 48 months, including evaluation development and setup; baseline, midline, and endline assessments; intervention implementation (24 months); laboratory measurements of biomarkers; and statistical analysis. The main study assessments will be conducted during monsoon cultivation (July-December) with a brief survey also conducted after the monsoon harvest (January-February). The same random subset of households enroled at baseline from each cluster will be followed at 12 and 24 months post-baseline assessment.

### Selection of clusters and random allocation procedures

A list of clusters in which APCNF has not yet been implemented will be provided by RySS and the evaluation team will randomly select clusters for inclusion in the BLOOM study from this list using simple random sampling. By purposefully enrolling clusters where RySS has never before worked, we will minimise what has been described elsewhere as the ‘[NGO] reputation effect’ [83]. In a previous randomised controlled trial in India, this reputation effect–meaning prior engagement with target communities–was shown to bias intervention effectiveness by at least 30% [83].

The study will be explained to elected representatives in the village as well as other stakeholders (e.g., community health workers and Anganwadi [government childcare centre] workers) and their permission sought. Given the narrow agricultural season window, clusters will be randomised to intervention or control after recruitment and enrolment, and the list shared in confidence with RySS so that they can begin planning implementation activities for intervention clusters. No implementation activities will begin, and data collectors and participants will not be informed of the randomisation status, until the baseline assessment is complete. Randomisation will be stratified by original district (Kurnool and Vishakhapatnam).

### Selection of evaluation participants

The sample will be selected via random selection of 34 households per cluster from a roster of households in each cluster with a child <3 years of age. Rosters will be obtained by conducting a comprehensive household listing in each cluster based on lists provided by Anganwadi workers. In the event that a cluster has fewer than 34 eligible households, all eligible households will be enroled.

Three participants will be enroled from each household: an adult male, adult female, and child. The parents of the child, if eligible, will be enroled. Eligibility criteria are summarised in Table 3. If one or both parents of the child are not available or not eligible, we will enrol the oldest eligible male or female in the household. If more than one child is eligible in a given household, we will enrol the oldest eligible child.

**Table 3 pone.0281677.t003:** Participant eligibility criteria for the BLOOM (co-Benefits of Largescale Organic farming On huMan health) study, a cluster-randomised controlled evaluation of Andhra Pradesh Community-managed Natural Farming in India.

	Adults	Children
**Inclusion criteria**	1. Household engaged in agriculture work defined as any one or more of the following: owning land, harvesting a crop in the past month regardless of land ownership, or earning a daily wage or contract-based wage for agricultural activities. This includes farmers, farm owners, farm workers, field workers, growers, harvesters, packers, graders and sorters, as well as agricultural pesticide handlers (mixers, loaders, cleaners and sprayers). 2. Aged ≥18 years. Age will be confirmed by directly viewing a government-issued document with the individual’s date of birth. 3. Permanently reside in the selected household. ‘Residence’ will be defined as a group of people who eat from the same kitchen. 4. Have a child aged <38 months old who also resides in the household. 5. Willing to provide informed consent.	1. Aged <38 months. Age will be confirmed by directly viewing a government-issued document with the child’s date of birth. 2. Permanently reside in the selected household. ‘Residence’ will be defined as a group of people who eat from the same kitchen. 3. Parent or legal guardian willing to provide informed consent.
**Exclusion criteria**	1. Plan to move permanently out of the study area in the next 12 months. 2. Visible disabilities (e.g., physical malformations or genetic syndromes) that prohibit participation. 3. Primary language other than Telugu. 4. Already enroled in a different research study. 5. Unwilling to provide informed consent.	1. Visible disabilities (e.g., physical malformations or genetic syndromes) that prohibit participation. 2. Already enroled in a different research study. 3. Parent or legal guardian unwilling to provide informed consent.

Each participant will have data collected at three time points: baseline, 12 months, and 24 months (Fig 3). Data at each time point will be collected over the course of four waves. During wave 1, written informed consent will be obtained from participants, participants will be screened for eligibility, and individual questionnaires will be administered (demographics, tobacco and alcohol use, clinical history including medication use, and depressive symptoms). During wave 2, two urine samples and one fasting blood sample will be collected from up to 12 households per cluster, and dietary intake, infant and young child feeding, and time use will be assessed in all households (coincident with the urine sample collection). During wave 3, physical measurements will be taken (blood pressure, weight, and length/height), child development will be assessed, and individual questionnaires will be administered (household economics and women’s empowerment). Finally, during wave 4, individual questionnaires will be administered (clinical symptoms and musculoskeletal pain, agricultural practices, and pesticide use). Household questionnaires (e.g., household economics and agricultural practices) will be administered to the head of household and the child development and infant and young child feeding questionnaires to the primary caregiver. A health report will be given to participants during waves 2 and 3. The assessments for each wave will last no longer than 2 hours. In the event that previously undiagnosed health conditions are identified (e.g., hypertension, anaemia, type 2 diabetes, severe wasting, or suicidal ideation), participants will be referred to the nearest health centre.

**Fig 3 pone.0281677.g003:**
[figure not shown]
Schedule of enrolment, intervention, and assessments for the BLOOM (co-Benefits of Largescale Organic farming On huMan health) study, a cluster-randomised controlled evaluation of Andhra Pradesh Community-managed Natural Farming in India. ‘M’ is adult male, ‘F’ is adult female, and ‘C’ is child in enrolled households.

### Blinding

It is not possible to blind participants to the intervention. Laboratory technicians and statistical analysts will be blinded. Field staff who collect the data will not be involved in intervention implementation.

### Primary outcomes

Urinary pesticide metabolites at 12 months in a 15% random subsample of adult men enroled in the study. Six common dialkylphosphate (DAP) metabolites of organophosphorus insecticides will be measured in an equal-volume composite urine sample consisting of two spot urine samples collected within a one-week period. Compositing samples reduces intra-person variability. The six DAPs will include: dimethylphosphate (DMP), dimethylthiophosphate (DMTP), dimethyldithiophosphate (DMDTP), diethylphosphate (DEP), diethylthiophosphate (DETP), and diethyldithiophosphate (DEDTP). Together, these six DAPs cover approximately 77% of organophosphorus insecticides produced in India (Table 4) [11]. Total DAP molar weight (∑DAPs) will be calculated by multiplying the concentration of each of the six DAPs by the molar weights of the respective DAP and summing them. Specific gravity-adjusted ∑DAPs will be analysed as the primary outcome. Specific gravity will be measured in the composite urine sample using a handheld refractometer (Atago PAL-10S). Urine aliquots will be shipped on dry ice to the laboratory for analysis in random sequence using gas chromatography-mass spectrometry (GC-MS) [84]. Laboratory technicians will be blinded to the randomisation status of samples.Urinary pesticide metabolites at 12 months in a 15% random subsample of adult women enroled in the study. The same method, as described above for adult men, will be used to assess specific gravity-adjusted ∑DAPs in adult women.Urinary pesticide metabolites at 12 months in a 15% random subsample of children enroled in the study. The same method, as described above for adult men, will be used to assess specific gravity-adjusted ∑DAPs in children.Dietary diversity score at 12 months in all adult men enroled in the study. Dietary intake of adults will be assessed using a single 24-hour dietary recall. Participants will be taken through the previous day from morning to evening and asked to recall all foods and beverages consumed and the portion size. A standard set of locally appropriate plates, bowls, and cups and show cards will be used to aid portion size estimation. Dietary diversity will be calculated using the FAO’s Minimum Dietary Diversity for Women (MDD-W) [85]. Ten food groups are included: (1) starchy staples (rice, wheat, and potatoes), (2) legumes and pulses, (3) nuts and seeds, (4) dark green leafy vegetables, (5) vitamin-A rich fruits and vegetables, (6) other vegetables, (7) other fruits, (8) dairy products, (9) eggs, and (10) flesh foods (meat, poultry, and fish). For analysis, men who consume a food group on the previous day will be assigned a value of 1 and those who do not will be assigned a value of 0 and the values across these ten food groups will be summed in a dietary diversity score. Thus, the dietary diversity score can range from 0 to 10 with 10 representing maximum dietary diversity.Dietary diversity score at 12 months in all adult women enroled in the study. The same method, as described above for adult men, will be used to assess dietary diversity in adult women.Dietary diversity score at 12 months in all children enrolled in the study. Dietary intake of children will be assessed using the standard WHO Infant and Young Child Feeding practices survey [86], adapted to the local context and administered to the primary caregiver of the child. Dietary diversity will be calculated using the WHO’s dietary diversity score (DDS). Whilst this was originally developed for children 6–23 months old, DDS can serve as an adequate proxy for micronutrient intake in children 24–59 months as well [87]. Eight food groups are included: (1) breast milk, (2) grains, roots, tubers, and plantains, (3) pulses, nuts, and seeds, (4) vitamin-A rich fruits and vegetables, (5) other fruits and vegetables, (6) dairy products, (7) eggs, and (8) flesh foods (meat, poultry, and fish). For analysis, children who consume a food group on the previous day will be assigned a value of 1 and those who do not will be assigned a value of 0 and the values across these eight food groups will be summed. Thus, DDS can range from 0 to 8 with 8 representing maximum dietary diversity.

**Table 4 pone.0281677.t004:** Top organophosphorus insecticides produced in India and their potential dialkyl phosphate metabolites.

	DMP	DMTP	DMDTP	DEP	DETP	DEDTP
Acephate	X	X				
Chlorpyriphos				X	X	
Dimethoate	X	X	X			
Ethion				X	X	X
Malathion	X	X	X			
Monocrotophos	X					
Temephos	X	X				

Abbreviations: dimethylphosphate (DMP), dimethylthiophosphate (DMTP), dimethyldithiophosphate (DMDTP), diethylphosphate (DEP), diethylthiophosphate (DETP), and diethyldithiophosphate (DEDTP).

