### Collection and storage of biological specimens

Urine and blood samples will be collected at three time points from adults, and urine at three time points for children in up to 12 households per cluster. Sample aliquots will be stored at -80°C in New Delhi, India at the Public Health Foundation of India’s biospecimens repository.

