### Power calculations

Power calculations were conducted using PASS 2019, v19.0.6 (NCSS, Kaysville, Utah, USA), accounting for the cluster-randomised design. Whilst hypotheses for the two primary outcomes (urinary pesticides and dietary diversity) were independent, in order to be conservative, a Bonferroni correction was applied (0.05/2, which is the number of primary outcomes) resulting in a two-sided alpha level of 0.025. It is expected that approximately 20% of the baseline sample will be loss-to-follow-up at 12 months. Two previous surveys in Andhra Pradesh by study team members had much lower loss to follow-up rates [2% from 2019 to 2020 in the SHEFS (Sustainable and Healthy Food Systems) nutrition survey (unpublished) and 10% for the mWellcare trial [104] but a higher rate was anticipated for the BLOOM study due to COVID-19.

Power for the primary outcomes is given in Table 5, which summarises the minimal detectable difference in mean levels associated with 80% power, a type I error rate alpha of 0.025, an intra-cluster correlation of 0.02, and 20% loss to follow-up. For ∑DAPs power calculations are shown for 150 per arm (a 15% subsample). Results in Table 5 confirm that the study is adequately power to detect a smaller difference than has been previously reported in the literature for these outcomes.

**Table 5 pone.0281677.t005:** Minimum detectable mean difference, with 80% power, alpha = 0.025, and intra-cluster correlation of 0.02.

	Standard Deviation for Mean Change in Outcome	Sample Size per Group	Minimum Detectable Mean Difference	Previous Study Estimate (95% Confidence Interval)
Change in mean ∑DAPs, adult men	111 μmol/l*	150	39.6 μmol/l (~55% of estimated baseline levels*)	-88% (not reported)^†^
Change in mean ∑DAPs, adult women	111 μmol/l*	150	39.6 μmol/l (~55% of estimated baseline levels*)	-88% (not reported)^†^
Change in mean ∑DAPs, children	17.3 nmol/l^‡^	150	6.17 nmol/l (~9.7% of estimated baseline levels^‡^)	-42.7% (-76.3–38.7)^‡^ -39.9% (-58.6, -12.6)^§^
Change in mean dietary diversity score, adult women	1.57^¶^	1000	0.29	0.36 (0.03–0.69)^¶^
Change in mean dietary diversity score, children	1.40^#^	1000	0.26	0.39 (0.13–0.64)^#^

* From an observational study of adult agricultural labourers in North Carolina [105].

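### The ∑DAPs subsample is defined on enrolled participants and given as 150 per arm, but Table 5's detectable differences need about 150 or more per arm after the expected 20% loss

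*Protocol article*

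**What the plan says.** All references are to the protocol article.

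- **Primary outcomes** defines the first ∑DAPs outcome as "Urinary pesticide metabolites at 12 months in a 15% random subsample of adult men enroled in the study". Women and children have parallel definitions, so three of the six listed primary outcomes rest on this subsample.
- **Power calculations** shows the ∑DAPs rows of Table 5 for 150 per arm and calls this a 15% subsample. It adds that "It is expected that approximately 20% of the baseline sample will be loss-to-follow-up at 12 months". Table 5 as a whole is said to rest on "a type I error rate alpha of 0.025, an intra-cluster correlation of 0.02, and 20% loss to follow-up".
- **Selection of evaluation participants** says that at each time point "two urine samples and one fasting blood sample will be collected from up to 12 households per cluster". **Collection and storage of biological specimens** states that "Sample aliquots will be stored at -80°C in New Delhi, India".
- **Statistical analysis plan** takes as its effect the between-group difference in change from baseline to 12 months. It plans a complete-case analysis with inverse probability weights for loss to follow-up.

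The article does not say when the 15% is drawn, whether it is limited to participants with urine at both visits, or whether 150 is counted before or after loss.

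**The concern.** The effect of interest is a change, so precision depends mainly on how many participants have ∑DAPs at both visits. A subsample taken as a share of those enrolled shrinks with follow-up. Table 5 says 20% loss is built into every row. If the ∑DAPs rows in fact assume that all 150 are analysed, the stated power for the three primary outcomes with the smallest samples is too high.

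The gap would also be avoidable. Far more urine is collected and frozen than the 15% needs, so the assay set could be drawn from participants who already have both samples.

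**Working it through.** **Inputs.** From Table 5: SD of change 111 μmol/l (adults) and 17.3 nmol/l (children) for ∑DAPs, and 1.57 (women) and 1.40 (children) for dietary diversity; listed n of 150 and 1000 per arm. From Power calculations: two-sided alpha 0.025, 80% power, ICC 0.02, 20% loss. From Study design: 80 clusters allocated 1:1, so 40 per arm.

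**Formula.** MDD = (2.241 + 0.842) × SD × √(2 × DEFF / n), with DEFF = 1 + (n/40 − 1) × 0.02. This is the normal approximation (z). The t version takes power from the noncentral t with 78 degrees of freedom (80 clusters less 2).

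**Step 1: dietary rows (stated 0.29 and 0.26).**

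| n per arm | DEFF | Women, z / t | Children, z / t |
|---|---|---|---|
| 1000 | 1.48 | 0.263 / 0.268 | 0.235 / 0.239 |
| 800 | 1.38 | 0.284 / 0.289 | 0.254 / 0.258 |

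The printed values appear at 800 with the t version. At 1000 neither version reaches them. For these rows, the listed n is therefore the number before loss.

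**Step 2: ∑DAPs rows (stated 39.6 and 6.17).**

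| n analysed per arm | Adults, z / t | Children, z / t | Power at 39.6 (z) |
|---|---|---|---|
| 120 | 45.1 / 45.8 | 7.02 / 7.14 | 68% |
| 135 | 42.6 / 43.3 | 6.64 / 6.75 | 73% |
| 150 | 40.6 / 41.3 | 6.33 / 6.43 | 78% |
| 160 | 39.4 / 40.0 | 6.14 / 6.24 | 80% |
| 163 | 39.0 / 39.7 | 6.08 / 6.18 | 81% |

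Without a design effect, 150 gives 39.5 and 6.16 (z). The stated values thus correspond to about 150 to 160 analysed, or about 164 on the t version that fits the dietary rows. On no version tried do they correspond to 120.

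**Step 3: what 15% yields.**

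- 15% of the pre-loss 1000 is 150. Less 20%, that is 150 × 0.8 = 120. The adult MDD is then 45.1/39.6, or 14% above the stated value.
- 15% of full planned enrolment is 0.15 × 34 × 40 = 0.15 × 1360 = 204. Less 20%, that is 163, and there is no shortfall.

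**Step 4: stored pairs available.** At most 12 × 40 = 480 per arm for each population. With 20% loss, 480 × 0.8 = 384. Both are upper figures, because collection is from up to 12 households and some clusters may have fewer.

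**Step 5: assay counts on the 120 reading, per arm and population.** The current definition needs 150 + 120 = 270 assays. Drawing 150 pairs needs 300 and lowers the adult MDD from 45.1 to 40.6, or 10%. Keeping 270 assays gives 135 pairs and 42.6, about 5.4% lower.

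**The case against.** A reader might infer that the assay set is fixed at enrolment and certain to fall to 120. The documents do not support that. The definition names the population sampled, not the date of the draw, and freezing urine from up to 12 households per cluster is compatible with a later draw. The Table 5 values for ∑DAPs themselves point to about 150 or more analysed, and 15% of 1360 would supply them. The fall to 120 is conditional on 150 being 15% of the same pre-loss 1000 that the dietary rows use.

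A reader might also infer that baseline assays on later dropouts are wasted. That goes too far: the planned GEE has a row per visit, so a baseline-only record may still inform the baseline group means. The article does not make clear whether complete-case means complete pairs.

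The 10% gain comes partly from extra assays; at an equal number of assays it is about 5.4%. Drawing from pairs selects on follow-up after randomisation, so it neither removes attrition bias nor settles the 24-month secondary outcome. Any claim that assaying in random sequence adds run-to-run error to each change has no figure behind it, since the article gives no run size.

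The timing of the draw could be left to a fuller document. What stands is that Table 5 states one loss assumption for all rows and its figures do not follow it consistently.

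**Conclusion.** The point holds in a limited form. Table 5 appears to take 20% off the 1000 but not off the 150, although the text applies the loss to both. If 150 is counted before loss, as 1000 is, about 120 pairs per arm remain. The detectable differences are then about 45.1 μmol/l and 7.02 nmol/l, with about 68% power at 39.6 instead of 80%. If the 15% applies to 1360 per arm, about 163 remain and the stated values stand, but the article would then be understating its subsample. These figures rest on the protocol's own SDs and ICC and on equal loss in urine and other households.

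The consequence is moderate. Table 5 equates 39.6 with about 55% of baseline, which implies a baseline of 72, so 45.1 is about 63%. That is still below the 88% difference cited for adults. The issue is misstated power and avoidable imprecision in three primary outcomes, not a design that cannot work.

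**What to change.** Define the ∑DAPs assay set as 150 pairs per arm in each of the three populations. Draw it at random, stratified by cluster and blind to arm, from urine-household participants with composites at both baseline and 12 months. Estimate the planned loss-to-follow-up weights from all participants with baseline urine, and add sampling weights if the fraction drawn differs by cluster. State how the same set will be used at 24 months.

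If the draw is not changed, say when it is made and whether 150 is before or after loss, and restate the ∑DAPs detectable differences for the number left after 20% loss.

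**Cost.** Baseline ∑DAPs results come later. For 150 pairs there are about 30 more assays per arm and population, or 30 × 2 × 3 = 180 in all. Holding the total at 270 per arm and population adds none and gives 135 pairs. No extra participants or visits are needed. The draw is possible only if the baseline aliquots have not yet been assayed, which the article does not state. Assaying a participant's two samples in the same GC-MS run is an optional laboratory step with no quantified gain.

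### The rule given for ∑DAPs multiplies by molar weight, so it cannot yield the molar sum in which Table 5 expresses this primary outcome

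*Protocol article*

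**What the plan says.** The protocol article, Methods, Primary outcomes, lists six DAP metabolites and combines them into one number. The definition opens "Total DAP molar weight (∑DAPs) will be calculated by multiplying" and gives the operation as "calculated by multiplying the concentration of each of the six DAPs by the molar weights of the respective DAP and summing them". The article then states: "Specific gravity-adjusted ∑DAPs will be analysed as the primary outcome". The same method "will be used to assess specific gravity-adjusted ∑DAPs in adult women" and "will be used to assess specific gravity-adjusted ∑DAPs in children". The definition therefore governs three of the six listed primary outcomes, and also the 24-month pesticide outcomes listed as secondary.

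The article does not state the unit in which the laboratory reports the six concentrations.

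In Power calculations, Table 5 expresses ∑DAPs in molar concentration. The minimum detectable difference is "39.6 μmol/l (~55% of estimated baseline levels") for adults and "6.17 nmol/l (~9.7% of estimated baseline levels") for children. In Statistical analysis plan, Equation 1 models the outcome with no transformation shown, and its group-by-time coefficient is a difference in change in the outcome's own units.

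**The concern.** A molar concentration is obtained from a mass concentration by dividing by molar weight. The article multiplies. The text is explicit, so this is not a detail left to a fuller document, and no other part of the article corrects it.

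Two things are at stake. The first is scale: an estimate computed by this rule could not be set against the minimum detectable differences in Table 5. The second is weighting: a molar sum counts each mole of each metabolite once, whereas the stated rule counts heavier metabolites more. Table 4 shows why the mix can matter. Monocrotophos yields only DMP, the lightest of the six, while chlorpyriphos yields DEP and DETP.

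**Working it through.** **1. The article's own figure.** The text says "For ∑DAPs power calculations are shown for 150 per arm (a 15% subsample"). The inputs from Table 5 and its text are SD 111 μmol/l (adults) or 17.3 nmol/l (children), two-sided alpha 0.025 and power 80%. The formula is

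minimum detectable difference = SD × √(2 × DE / n) × (z₀.₉₈₇₅ + z₀.₈₀), with DE = 1 + (m − 1) × ICC and z-sum 2.241 + 0.842 = 3.083.

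- n = 150, no design effect: 111 × √(2/150) × 3.083 = 39.5; 17.3 × √(2/150) × 3.083 = 6.16.
- n = 160 (4 in each of 40 clusters), ICC 0.02, DE = 1.06: 39.4 and 6.14.
- n = 150, ICC 0.02, DE = 1.055: 40.6 and 6.33.

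The printed 39.6 and 6.17 are reproduced closely by the first two. The calculation runs entirely in molar units and never uses the ∑DAPs formula, so correcting the formula does not change it. Whether the adult rows should be in μmol/l when the child row is in nmol/l is a separate question. Both are molar units, which is all this point needs.

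**2. Units of the rule as written.**

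- Inputs in mass concentration: (μg/l) × (g/mol) = μg·g/(l·mol). This is neither molar nor mass concentration.
- Inputs already molar: (nmol/l) × (g/mol) = ng/l. This is a mass sum.

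Neither gives nmol/l or μmol/l. Specific-gravity adjustment does not help: specific gravity has no unit, and one sample-specific factor applies to all six metabolites alike.

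**3. Relative weights.** Molar weights M are computed from the chemical formulae (C 12.011, H 1.008, O 15.999, P 30.974, S 32.06). They are an assumption in the sense that the article does not list them. In a true molar sum each mole has weight 1. Under the rule as written, the weight per mole relative to DMP is (M/M_DMP)² for mass inputs and M/M_DMP for molar inputs.

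| Metabolite | M (g/mol) | Mass inputs | Molar inputs |
|---|---|---|---|
| DMP | 126.05 | 1.00 | 1.00 |
| DMTP | 142.11 | 1.27 | 1.13 |
| DEP | 154.10 | 1.49 | 1.22 |
| DMDTP | 158.17 | 1.57 | 1.25 |
| DETP | 170.16 | 1.82 | 1.35 |
| DEDTP | 186.22 | 2.18 | 1.48 |

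**4. Scale.** With μg/l inputs, the correct value is 1000/M nmol/l per μg/l and the rule gives M, so the number is M²/1000 times the nmol/l value: 126.05²/1000 = 15.9 for DMP and 186.22²/1000 = 34.7 for DEDTP. With 1 μg/l of each metabolite, dividing gives 7.93 + 7.04 + 6.32 + 6.49 + 5.88 + 5.37 = 39.0 nmol/l, and multiplying gives 936.8 μg·g/(l·mol).

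**5. Effect on a percentage reduction (illustrations, all six metabolites).**

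| Assumed change | Equal μg/l of each: molar sum | As written | Equal nmol/l of each: molar sum | As written |
|---|---|---|---|---|
| Dimethyl DAPs fall 50% | 27.3% | 22.8% | 25.0% | 22.8% |
| Diethyl DAPs fall 50% | 22.7% | 27.2% | 25.0% | 27.2% |
| All six fall 50% | 50% | 50% | 50% | 50% |

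The as-written figures are half the share of summed M: 0.5 × 426.33/936.8 = 22.8% (dimethyl) and 0.5 × 510.48/936.8 = 27.2% (diethyl). The molar-sum figures in the first pair of columns are half the share of the 39.0 nmol/l: 0.5 × 21.29/39.03 = 27.3% and 0.5 × 17.74/39.03 = 22.7%.

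**6. Agreement between the two versions.** In simulated lognormal mass concentrations with equal medians (assumed log-SD 0.8 or 1.2, between-metabolite correlation 0 to 0.6), the sum as written and the molar sum correlate at about 0.97 to 0.997.

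**The case against.** The strongest reply is that this is a slip in one sentence of a condensed article. The molar units of Table 5 show that a molar sum was intended, and the article says that standard operating procedures will document the methods in detail. That may well be so, and nothing in the article shows that the trial would compute the outcome this way. But the sentence is the article's only definition of this outcome. An analyst who follows it computes the wrong quantity, and one who silently corrects it departs from the published definition.

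Other limits are sound and narrow the point:

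- A reader might infer that every metabolite is over-weighted by the square of its molar weight. That holds only for mass inputs, and the article does not give the unit. With molar inputs the weights are first-power, at most 1.48.
- A reader might infer that ethyl metabolites as a class are favoured over methyl ones. The table does not bear this out: DMDTP (methyl) is heavier than DEP (ethyl). The distortion follows molar weight.
- A reader might infer that the comparison between arms is invalid or the trial under-powered. The same fixed weights apply in both arms, so if the programme changes no metabolite the test remains valid, and the sample size never used the formula.
- The programme aims at zero synthetic inputs, so a broad fall is the planned mechanism. The article does not say that a shift between organophosphates is expected.
- The previous-study column of Table 5 is in percentages for ∑DAPs, and the adult comparator is a different metabolite. The loss of comparability therefore concerns absolute values chiefly.

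**Conclusion.** The point holds as an error in the stated definition of three of the six primary outcomes. Whatever unit the laboratory reports, multiplying by molar weight does not give the molar sum used in Table 5. This follows from the units alone and needs no outside figure.

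Its numerical size rests on molar weights taken from the chemical formulae and on the unknown reporting unit: up to 2.18-fold mis-weighting relative to DMP with mass inputs, up to 1.48-fold with molar inputs. In the six-metabolite illustrations a percentage reduction moves by about 2 to 5 percentage points when only one group of metabolites falls, and not at all when all fall in proportion. The absolute difference-in-differences estimate would be off the Table 5 scale in every case. The expected distortion of the percentage effect is moderate, but the definition should be corrected before the outcome is derived.

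**What to change.** State the unit in which the laboratory reports each DAP, and replace the sentence with a rule that depends on it, for example:

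> ∑DAPs is the sum of the molar concentrations of the six DAPs. If the laboratory reports mass concentration (μg/l), each value is divided by its molar weight (g/mol) and multiplied by 1000 to give nmol/l before summing. If it reports molar concentration, the values are summed with no molar-weight factor. The sum is then adjusted for specific gravity and reported in molar units.

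The condition is needed because dividing values that are already molar would introduce a new error. Check that the analysis code does the same for men, women and children at each time point. The cost is one sentence and a check of the derivation code. Sampling, assays and sample size do not change.
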